### Plans to Give Access to the Full Protocol, Participant-Level Data, and Statistical Code

This decision is subject to approval by the Physiotherapy Department of the University of Pretoria, South Africa.

### Oversight and Monitoring

The trial is conducted by a team of 2 qualified physiotherapists and 2 trained research assistants, while the investigator and research supervisors monitor and oversee data collection and analysis. The intervention administrator provides daily updates regarding the trial to the chief investigator who then provides weekly updates to his supervisors. Challenges encountered during the trial are resolved by the investigators through conference meetings or other feasible alternatives.

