### Trial Design

This is a parallel randomized controlled trial employing a restricted assignment scheme, where participants were allocated in a 1:1 ratio. The intervention is aerobic exercise, and the comparator is a no-treatment control group. All assessors will be blinded regarding participant identification of both the experimental and control groups.

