## Methods

### Study Setting

This study is taking place at the Exercise Immunology Clinic of the Department of Physiotherapy, University of Nigeria Teaching Hospitals (UNTH) Ituku-Ozalla, Nigeria, and the University of Nigeria Enugu Campus (UNEC). A preliminary study revealed that approximately 50% of the prospective participants that visited the UNTH ART clinic were from Enugu Metropolis. The second site, UNEC, was chosen as a more centralized location for participants who resided in Enugu Metropolis and nearby environs. Participants were purposively selected to participate. To ensure consistency, the intervention team, which is comprised of 2 qualified physiotherapists and 2 trained research assistants, was trained by the principal investigator.

We identified prospective participants during a pilot study. Prospective participants, who lived in the Enugu metropolis and surrounds, were invited by text message to attend the ART clinic. Only participants able to travel to the study site with ease were invited to participate. Participants were randomly assigned to the intervention or control group. First, a sequence of random numbers was generated using Random Restricted Software 2.0. An independent person assigned the random numbers to either the intervention or control group by placing the generated numbers into A4, opaque, sealed envelopes, with only C or E written on an inconspicuous area of the envelope. Envelopes with C are control and E are exercise. The outcome assessors (the principal investigator and clinical psychologist) enrolled participants into the study, without knowing group assignments. Outcome assessors, including the principal investigator, neurologist and clinical psychologist, and data analyst, were also blinded while conducting neurological assessments. Care physicians were asked not to suggest any form of aerobic exercise to the patients throughout the study period. Trained physiotherapists conducted the treatment. Finally, the data were coded (C for control group and B for experimental group) so that the biostatistician will not know which group is experimental or control.

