### Neuropsychological Screening

The principal investigator (who is a physiotherapist working with people living with HIV and neurological conditions), a clinical psychologist, and a neurologist (who is a specialized medical doctor) conduct the neuropsychological screening, which is conducted in 3 stages. First, we conduct a brief neuromedical screening using a pilot assessment guide; then, we administer the neuropsychological instruments and, finally, assess the subjective symptoms of HAND such as difficulty remembering recent events (people, conversations, names, commitments, where things are placed), understanding conversation or reading materials, word finding, planning activities, problem solving, concentrating, thinking clearly or logically, finding his or her way about, calculating, and following direction or instruction.

We administer neuropsychological instruments chosen for their simplicity and ease of administration in any language. Only the Hopkins Verbal Learning Test-Revised (HVLT-R) and Controlled Oral Word Association Test (COWAT) require understanding of some English words. These tests were extracted from the international neurobehavioral test battery used by the HIV Neurobehavioral Research Center [1] and a recent clinical trial on HAND [50,51]. These tests are sensitive to HAND in Nigeria [52,53]. We first screen for probable dementia using the International HIV Dementia Scale (IHDS). Confirmatory neuropsychological tests are administered in the following order: first, we administer the HVLT-R immediate recall (duration 3-5 minutes). After waiting 20 minutes to 25 minutes to administer the second part of the HVLT-R, we administer the Trail Making Test (TMT)-A and -B (5-10 minutes), verbal fluency (3-8 minutes), and the Digit Span Test (5-10 minutes). We then administer the HVLT-R delay recall. We also assess neurocognitive performance in line with the 2007 modified American Academy of Neurology criteria, also known as the Frascati criteria [1,54]. We will convert the raw scale scores using a clinical rating algorithm, to sum the scores to obtain an overall score for each participant. The latter will be used for covariate analysis, if needed.

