### Data Management

Data are manually transcribed from paper forms into a Microsoft Excel spreadsheet and exported and secured to MicrOsiris 24.8. Data are verified through independent double data entry, where the principal investigator (data manager) and a data clerk both enter data. Consistency checks are performed during data entry, and warnings are displayed when needed.

Personal information such as contact number and identity number are collected and only used to reach participants when necessary and for possible access to participants’ hospital files. Data are handled confidentially and are not shared with a third party. Participants’ names do not appear in any data record except in a case of referral.

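### The stated blinding of assessor and analyst is not protected as written: the assessing principal investigator has roles that can reveal allocation, and the analysis code keeps C for control

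*Protocol article*

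**What the plan says.** On assessors, the Trial Design section of the protocol article states: "All assessors will be blinded regarding participant identification of both the experimental and control groups". Study Setting repeats this by role: "The outcome assessors (the principal investigator and clinical psychologist) enrolled participants into the study, without knowing group assignments", and then "Outcome assessors, including the principal investigator, neurologist and clinical psychologist, and data analyst, were also blinded while conducting neurological assessments". Neuropsychological Screening confirms who does the testing; it lists "The principal investigator (who is a physiotherapist working with people living with HIV and neurological conditions), a clinical psychologist, and a neurologist".

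Two later sections give the lead investigator further duties. Data Management describes double entry in which "the principal investigator (data manager) and a data clerk both enter data". Oversight and Monitoring says that "the investigator and research supervisors monitor and oversee data collection and analysis", and adds: "The intervention administrator provides daily updates regarding the trial to the chief investigator who then provides weekly updates to his supervisors".

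On the analyst, Study Setting reports that "the data were coded (C for control group and B for experimental group"), and gives the purpose as keeping the biostatistician unaware of which group is which. Earlier in the same section the allocation envelopes are marked C for control and E for exercise.

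**The concern.** Exercise is compared with no treatment, so participants know their arm. Blinding of the people who test, classify and analyse is therefore the main protection left for the neurocognitive outcomes, which Study Outcomes lists as primary (performance and prevalence of HAND). If the assessor learns the arm before the post-intervention assessments, the parts that depend on the examiner could drift in favour of exercise. If the analyst knows the arm, the open decisions in Statistical Methods (which covariates to use, how to handle missing data) are no longer made blind. In both cases the report would claim a safeguard that the described procedures do not secure.

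**Working it through.** No figure in the article is in dispute. The one design calculation reproduces: a two-sample t test with difference 13.4, SD 16.67, two-sided 5% and 90% power needs 33.51 per group, rounded up to 34 (68 in total), and power at 34 per group is 0.904. The point does not depend on it. The check is a comparison of sections.

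**Analyst code**

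| Item (Study Setting) | Control | Exercise |
|---|---|---|
| Envelope letter | C | E |
| Analysis data letter | C | B |

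Only the exercise letter was changed. The control letter is still the initial of the word and the letter on the envelope, and with two groups, identifying one identifies the other. The article also prints the key, while its Results section says that analysis has not yet been done. This part needs no inference.

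**Principal investigator's roles**

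1. Blinded outcome assessor: Study Setting and Neuropsychological Screening, explicit.
2. Data manager and one of two people entering data: Data Management, explicit. Which forms, and whether they carry arm labels, is not stated. The trial data include exercise adherence (a covariate in Statistical Methods) and two-weekly adverse-event forms (Adverse Event Reporting and Harms). The first points to the exercise arm by its nature; the second may.
3. Recipient of daily updates: Oversight and Monitoring, but under the title of chief investigator. The article describes one lead investigator who reports to supervisors and names no separate chief investigator, so reading the two as one person is natural. It remains an inference.

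**Could the updates reveal the arm?** Under Exercise Intervention, each exercise participant attends 3 × 12 = 36 sessions. Under Control Group, two education sessions are described. Daily reports from the person who runs the intervention will therefore tend to concern exercise participants. Their actual content is not given.

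**Is there a barrier?** None is stated: no arm-neutral reporting, no separation of session records from the assessors. Study Setting limits the blinding claim to the time of the neurological assessments. That does not help, because the assessments after 12 weeks and 3 months after the intervention come after the updates.

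**Which outcomes are exposed?**

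- Examiner-dependent: the symptom interview, the Frascati classification, and the Trail Making Test, a timed task in which the examiner points out errors and guides their correction.
- Less exposed: counts of words or digits (HVLT-R, COWAT, Digit Span Test).
- Little exposed: CD4 count and viral load, analysed by the clinic's laboratory scientist.

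**Would neutral codes be enough for the analyst?** Not alone. Exercise adherence is a planned covariate, so a dataset that contains it can reveal the arm under any code.

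**The case against.** The strongest reply is that the article shows no unblinding. The updates could be purely logistical, the forms could be coded, and a condensed article commonly leaves such workflow to the full protocol. Most of the tests yield counts or times, and testing is shared with a psychologist and a neurologist. Much of this stands, and it limits the point to a risk. It does not remove it: the article makes explicit blinding claims and then assigns roles that cut across them, which is more than missing detail. It also leaves the C/B code untouched.

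A reader might infer more than the text supports:

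- *That assessor blinding is impossible.* This would need the updates to identify participants or arms, and the chief investigator to be the principal investigator. Neither is stated.
- *That the principal investigator enters attendance and exercise records before assessing outcomes.* Data Management lists no forms and gives no timing.
- *That having trained the intervention team unblinds the principal investigator.* Training reveals no participant's allocation.
- *That the bias can be sized.* Assume, for example, a differential scoring bias of 0.2 SD. That is 0.2 × 16.67 = 3.33 points; the standard error is 16.67 × √(2/34) = 4.04; the shift is 0.825 standard errors; and the two-sided type I error would be about 13% instead of 5%. The arithmetic is right, but 0.2 is not in the article, Sample Size does not say which outcome its means and SD describe, and the calculation applies the bias throughout although three assessors are named.

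**Conclusion.** The point holds as two statements of different strength. First, the analysis code does not do what the article says it does; this follows directly from Study Setting. Second, the principal investigator's blinding as an assessor is unprotected. The data-management role is explicit. The daily-update route rests on the assumption that chief and principal investigator are the same person. If they are not, the data-entry overlap and the code defect remain.

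The consequence is a possible bias, most plausibly towards exercise, in the examiner-dependent parts of the cognitive outcome. Its size cannot be estimated from the article. The matter should be corrected because it bears on the credibility of a primary result and because analysis had not begun when the article was written.

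**What to change.** - **Analyst, still possible:** replace C/B with neutral codes whose key is held by the independent person who prepared the envelopes. Withhold exercise-adherence data from the analyst until the unadjusted comparison is locked, and release them for the adjusted analyses afterwards.
- **Assessments still to be done:** send intervention reports to the supervisors, or make them arm-neutral. Have the already named clinical psychologist and neurologist do the post-intervention cognitive assessments. Have non-assessors enter attendance and adverse-event forms (the data clerk and one other, so that double entry is kept).
- **Assessments already done:** report the principal investigator as potentially unblinded, instead of claiming that all assessors were blinded. Enrolment ended in May 2021, and the article does not say how many assessments remain, so this may be the larger part.
- **Text:** state whether the chief and principal investigator are the same person, and what the daily updates contain.

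The cost is a re-assignment of roles already named, a short change of text and a two-step data release; no new staff are needed. The downside is slightly more assessment load on the psychologist and the neurologist.

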### Adverse Event Reporting and Harms

Participants are asked to report any adverse event following exercise. Adverse events are formally assessed every 2 weeks using an adverse event form piloted by the US Medical Device and Diagnostic Industry recommendations [87,88] (Multimedia Appendix 13). If an adverse event is reported, the patient is referred to their physician for immediate assessment of underlying cause and possible management. A physiotherapist treats cases of pain, lower back pain, fatigue, and muscle soreness and prescribes rest to the participants when necessary. In cases of spontaneous but mild adverse events, patients are given sufficient time to rest, after which a therapist decides if the participant is fit to continue the scheduled exercise.

### Plans for Communicating Important Protocol Amendments to Relevant Parties

Amendments to the trial protocol with respect to eligibility criteria, outcomes, analysis, and frequency and duration of treatment will be communicated first to the researchers’ supervisors and then the University of Pretoria, Faculty of Health Sciences Research Ethics Committee, the PAN Africa Trial Registry, and the journal in which the protocol is published.

### Dissemination Plans

The outcome of the trial will be communicated to participants and health care professionals through conference presentations and to the general public through publication in a peer-reviewed international journal. No publication restriction applies. The data will be available for sharing upon request, which is subject to approval by the Department of Physiotherapy, University of Pretoria.

### Ethics Approval

Ethical approval was obtained from the University of Pretoria research ethics committee (Ethics reference no. 152/2020). Informed consent was obtained before enrollment. Prior to consent seeking, we introduced the study and explained the purpose thereof. Participants reserved the right to make decisions regarding their participation without inducement and such right was upheld throughout the study.

## Results

The trial, which secured funding in March 2020, was approved by the Institutional Review Board in May 2020. Data collection commenced in June 2020, with a pilot study to examine the rater reliability and minimum detectable change of the selected neuropsychological tests. Between July 2020 and November 2020, individuals with HAND had been identified. Participant enrollment commenced in January 2021 and was completed in May 2021. An amendment was submitted and secured ethical approval. Over 60% of the participants were recruited at the time of first submission to JMIR Mental Health. Data curation is still ongoing; hence, data analysis is yet to be executed. Study outcomes are expected to be published in March 2022.

## Discussion

In line with the ART clinic’s COVID-19 prevention guidelines, personal protective equipment including face masks and hand sanitizer are used by research team members and participants, while ensuring social distancing. When considering the acceptability of incentives in clinical trials, evidence suggests that incentives may ensure a good degree of adherence and completion [89-92]. Several systematic reviews [90-92] have argued that incentives cover opportunity costs of participating in behavioral interventions such as exercise. Participants will be compensated for transport money to the hospital only.

## Appendix

Multimedia Appendix 1 Beck Depression Inventory.

Multimedia Appendix 2 Alcohol Use Disorder Identification Test (AUDIT).

Multimedia Appendix 3 Drug Abuse Screening Test.

Multimedia Appendix 4 International HIV Dementia Scale.

Multimedia Appendix 5 Controlled Oral Word Association Test (COWAT) (Verbal Fluency Test).

Multimedia Appendix 6 Hopkin Verbal Learning Test-Revised.

Multimedia Appendix 7 Trail Making Test A & B.

Multimedia Appendix 8 Digit span test.

Multimedia Appendix 9 Lawton Instrumental Activities of Daily Living (IADL) scale.

Multimedia Appendix 10 The World Health Organization Quality of Life (WHOQoL) Bref.

Multimedia Appendix 11 Oxford Participation and Activities Questionnaire (Ox-PAQ).

Multimedia Appendix 12 Physical Activity Readiness Questionnaire.

Multimedia Appendix 13 Adverse events form.

## Abbreviations

ACSM: American College of Sports Medicine
ART: antiretroviral therapy
AUDIT: Alcohol Use Disorder Identification Test
BBB: blood-brain barrier
BDI: Beck Depression Inventory
BP: blood pressure
CD4: cluster of differentiation-4
COWAT: Controlled Oral Word Association Test
DST: digit span test
HAND: HIV-associated neurocognitive disorder
HR: heart rate
HRmax: age-predicted maximum HR
HVLT-R: Hopkins Verbal Learning Test-Revised
IHDS: International HIV Dementia Scale
NSFAS: National Student Financial Aid Scheme
Ox-PAQ: Oxford Participation and Activities Questionnaire
QoL: quality of life
TMT: Trail Making Test
UNEC: University of Nigeria Enugu Campus
UNTH: University of Nigeria Teaching Hospitals
VO_2_: maximum oxygen uptake
WHO: World Health Organization
WHOQOL: World Health Organization Quality of Life
YMCA: Young Men Christian Association
